## Abstract

**Background:**

Although beta-blockers improve clinical outcomes in heart failure with reduced ejection fraction, the benefit of beta-blockers in heart failure with preserved ejection fraction (HFpEF) is uncertain. Global longitudinal strain (GLS) is a robust predictor of heart failure outcomes, and recent studies have shown that beta-blockers are associated with improved survival in those with low GLS (GLS <14%) but not in those with GLS ≥14% among patients with LVEF ≥40%. Therefore, the objective of this trial is to evaluate the effect of sustained-release carvedilol (carvedilol-SR) on the outcome [N-terminal pro-B-natriuretic peptide (NT-proBNP) concentration] in patients with hypertension and HFpEF and will assess the differential effects of these drugs on the outcome, according to the GLS categories.

**Methods:**

This prospective randomized double-blind multicenter trial (CARE-preserved HF) will include 100 patients with HFpEF from three tertiary hospitals in South Korea. Patients with HFpEF and hypertension aged ≥20 years who have evidence of functional and structural heart disease on echocardiography and elevated natriuretic peptide will be enrolled. Eligible participants will be randomized 1:1 to either the carvedilol-SR group (*n* = 50) or the placebo group (*n* = 50). Patients in the carvedilol-SR group will receive 8, 16, 32, or 64 mg carvedilol-SR once daily for 6 months, and the dose of carvedilol will be up-titrated at the discretion of the treating physicians. The primary efficacy outcome was the time-averaged proportional change in N-terminal pro-B-natriuretic peptide concentration from baseline to months 3 and 6. We will also evaluate the differential effects of carvedilol-SR on primary outcomes according to GLS, using a cut-off of 14% or the median value.

**Discussion:**

This randomized controlled trial will investigate the efficacy and safety of carvedilol-SR in patients with HFpEF and hypertension.

**Clinical Trial Registration:**

ClinicalTrial.gov, identifier NCT05553314.

## Introduction

The prevalence of heart failure (HF) with preserved ejection fraction (HFpEF) is increasing (1–3). Approximately 50% of all HF patients have HFpEF, and in the general population aged ≥60 years, over 4% were identified with HFpEF (4–7). Beta-blockers are known to reduce mortality in HF with reduced ejection fraction (HFrEF) (8) and are recommended by current guidelines (9–11). However, the effects of beta-blockers on HFpEF remain controversial. The SENIORS randomized controlled trial, examining the effects of nebivolol on mortality and cardiovascular admissions, revealed an overall benefit in patients with an left ventricular ejection fraction (LVEF) >35% (12); however, the study had insufficient patients and events to draw any conclusions in those with a more preserved LVEF (LVEF ≥50%). In previous randomized clinical trials and meta-analyses, the effect of beta-blockers was not consistent in patients with HFpEF (13–16). Also, in many real-world cohorts, the use of beta-blockers in patients with HFpEF is not associated with improved clinical outcomes of HF (17, 18). Although a recent meta-analysis including 16 randomized trials or observational cohort studies showed that beta-blocker therapy reduces all-cause mortality in patients with HFpEF (15), the benefit of beta-blockers in HFpEF is considered unclear. In addition, a *post hoc* analysis of the TOPCAT trial showed that beta-blockers were associated with an increased risk of hospitalization for HF in patients with HFpEF (19). However, in real-world clinical practice or recent trials, a large proportion of patients with HFpEF are currently receiving beta-blockers (19–22), reflecting the potential benefits of beta-blockers in HFpEF through sympathetic antagonism, including lower blood pressure (BP) and heart rate (HR) and prolong diastolic filling time (16, 23).

Myocardial strain is based on the speckle-tracking method and is an emerging parameter for evaluating the systolic function of the heart in a more sophisticated manner than conventional methods (24, 25). In a recent study, Park et al. showed that left ventricular (LV) global longitudinal strain (GLS) was a better predictor of clinical outcomes than LVEF and that patients with similar GLS had similar prognoses, regardless of LVEF (26). Moreover, a significant proportion of patients with HFpEF have low GLS despite preserved LVEF (27). Recently, in a retrospective study of 1,969 patients with HF and LVEF of ≥40%, beta-blockers were associated with improved survival in those with low GLS (GLS <14%) but not in those with GLS ≥14% (28).

Because HFpEF is a heterogeneous and complex syndrome rather than a single disease entity (7), we hypothesized that GLS may be a factor determining the effects of beta-blockers in HFpEF. Carvedilol is a non-selective beta-blocker that has been extensively studied in patients with HFrEF (8, 29). Recently, sustained-release carvedilol (carvedilol-SR) has been developed, which can maintain an effective plasma concentration without exceeding the critical level for adverse effects (30). Carvedilol-SR has the advantage of being administered only once a day compared with the twice-daily administration of immediate-release carvedilol (carvedilol-IR). Therefore, this trial aim to evaluate the efficacy of carvedilol-SR on the outcome [N-terminal pro-B-natriuretic peptide (NT-proBNP) concentration] in patients with hypertension and HFpEF, and will assess the differential effects of these drugs on the outcome, according to GLS categories.

## Methods and analysis

### Study design

Sustained-release CARvedilol in patients with hypErtension and Heart failure with Preserved ejection fraction (CARE-preserved HF) is a multicenter, prospective, randomized, double blinded, phase 4 pilot study that assesses the efficacy of carvedilol-SR compared with placebo in patients with hypertension and HFpEF. The study flow chart is presented in Figure 1. Three tertiary university hospitals in South Korea participated in the study. Enrollment began in November 2021, is ongoing and is expected to be completed by early 2024. The trial design was registered at ClinicalTrial.gov (NCT05553314).

**Figure 1 F1:**
[figure not shown]
Study flowchart. Carvedilol-SR, sustained-release carvedilol.

### Study population

We have been enrolling patients with hypertension and HFpEF aged ≥20 years. Patients must have symptoms of HF and elevated natriuretic peptides at the screening visit: NT-proBNP ≥220 pg/ml [or B-type natriuretic peptide (BNP) ≥80 pg/ml] for patients with sinus rhythm (SR), or ≥660 pg/ml (or BNP ≥240 pg/ml) for patients with atrial fibrillation (AF). For the hypertension criteria: (1) patients' average systolic blood pressure (SBP) must be ≥140 mmHg or diastolic blood pressure ≥90 mmHg, obtained from BP measured three times on the reference arm in the sitting position at screening; (2) for those taking anti-hypertensive medications who are on stable antihypertensive dosage that has not been adjusted for 8 weeks, the SBP must be ≥110 mmHg. Patients with SBP <110 mmHg or resting HR <60 beats/min at the screening visit will be excluded. For the HFpEF criteria, we referred to the consensus recommendation of the Heart Failure Association of the European Society of Cardiology (31). LVEF should be ≥50% on echocardiography within 2 months before randomization. In addition, patients should have one or both of the following evidence of structural heart disease: (a) left atrial volume index ≥29 ml/m^2^ in patients with SR or ≥34 ml/m^2^ in patients with AF, (b) left ventricular mass index ≥115 g/m^2^ in males or ≥95 g/m^2^ in females. Patients should also have at least one indication of functional heart disease in terms of average E/e', septal and lateral e', peak tricuspid regurgitation velocity, and pulmonary artery systolic pressure. Patients will be excluded if they are taking any beta-blockers within 4 weeks prior to enrollment or if they have a contraindication to beta-blockers. Patients with severe chronic kidney disease (creatinine >2.4 mg/dl) or liver enzyme levels three times the normal upper limit will be excluded. Detailed inclusion and exclusion criteria are shown in Table 1.

**Table 1 T1:** Inclusion and exclusion criteria.

Inclusion criteria
1. ≥20 years of age, male or female 2. Patients with an SBP of ≥140 mmHg or a DBP of ≥90 mmHg, or if taking anti-hypertensive medication, an SBP of ≥110 mmHg. 3. Current symptom(s) of HF at screening visit^a^ 4. Elevated natriuretic peptides: NT-proBNP ≥220 pg/ml (BNP ≥80 pg/ml) for patients with SR or ≥660 pg/ml (BNP ≥240 pg/ml) for patients with AF at screening visit 5. LVEF ≥50% by echocardiography within 2 months before the randomization 6. Structural heart disease evidenced by one or both of the following echocardiography findings a) LAVI ≥29 ml/m^2^ in patients with SR or ≥34 ml/m^2^ in patients with AF b) LVMI ≥115 g/m^2^ in male or ≥95 g/m^2^ in female 7. Functional heart disease evidenced by at least one of the following echocardiography findings a) Average E/e’ ≥9 b) Septal e’ <7 cm/s c) Lateral e’ <10 cm/s d) Peak tricuspid regurgitation velocity >2.8 m/s e) Pulmonary artery systolic pressure >35 mmHg
Exclusion criteria
1. SBP <110 mmHg, or resting heart rate <60 beats/min at the screening visit 2. Patients who have a contra-indication to beta-blockers (including those with second-or third-degree atrioventricular block; respiratory diseases, including severe or uncontrolled asthma, chronic obstructive lung disease, allergic rhinitis or glottis edema; or severe peripheral vascular disease [Raynaud's syndrome, intermittent claudication]) 3. Patients who take any beta-blockers within 4 weeks before enrollment or who are expected to take another beta-blocker after randomization 4. Patients with a history of the following diseases - Amyloidosis, hypertrophic cardiomyopathy with left ventricular outflow tract obstruction, severe aortic or mitral valve stenosis, acute coronary syndrome within 3 months, percutaneous coronary intervention within 3 months, and recent cardiothoracic surgery within 3 months - Severe cerebrovascular events including ischemic stroke and hemorrhagic stroke within 6 months 5. Patients with significant kidney or liver disease - Creatinine >2.4 mg/dl or - Alanine transaminase or aspartate transaminase level is at least 3 times higher than the normal upper limit 6. Patients with a history of secondary hypertension or suspected secondary hypertension 7. Moderate-to-severe retinopathy (for example, retinal hemorrhage, visual disturbance, retinal microaneurysm within 6 months) 8. Patients in a clinical status that can significantly influence absorption, distribution, metabolism, and secretion of drugs for clinical trials: a. History of major gastrointestinal surgery, such as gastrectomy or gastric bypass surgery b. Inflammatory bowel disease within 12 months c. Current gastric ulcer, pancreatic function abnormality including pancreatitis, gastrointestinal/rectal bleeding which requires treatment d. Current urologic stenosis or obstruction which requires treatment 9. Chronic inflammatory diseases which require long-term use of anti-inflammatory treatment 10. Hypersensitivity to carvedilol 11. Patients with malignant disease including lymphoma and leukemia within 5 years 12. Patients who were prescribed other medication for any other clinical trials within the pre-analytical 28 days 13. Patients who are expected to have prolonged hospital stay due to other medical problems other than chronic heart failure (for example, femoral neck fracture) 14. Patients with a history of alcohol or drug abuse within the last 12 months 15. Patients with potential pregnancy or breastfeeding 16. Patients who are considered inappropriate by researchers to participate in the clinical trial

AF, atrial fibrillation; BNP, B-type natriuretic peptide; DBP, diastolic blood pressure; GLS, global longitudinal strain; HF, heart failure; LAVI, left atrial volume index; LVMI, left ventricular mass index; NT-proBNP, N-terminal pro B-type natriuretic peptide; SBP, systolic blood pressure; SR, sinus rhythm.

^a^
HF symptoms include dyspnea on exertion, paroxysmal nocturnal dyspnea, orthopnea, or leg swelling.

### Patient recruitment and randomization

Potential participants will be screened (visit 1) on an outpatient or inpatient basis (Figure 2). After a comprehensive interview, eligible participants will be asked to provide written informed consent to participate in the trial. A baseline survey of eligible participants covering demographics and cardiovascular comorbidities will be conducted by research nurses (Table 2). Then, using a web-based central randomization service (http://matrixmdr.com), eligible participants will then be randomly assigned to either the carvedilol-SR group or the placebo group in a 1:1 ratio (visit 2). The randomization block will be generated by an independent statistician unrelated to this study using the SAS randomization program.

**Figure 2 F2:**
[figure not shown]
Study design of CARE-preserved HF. Patients will be randomized to either carvedilol-SR group or placebo groups. Carvedilol-SR, sustained-release carvedilol.

**Table 2 T2:** Standard protocol items: recommendation for interventional trials (SPIRIT) checklist.

	Study period			
	Enrolment (screening)	Allocation	Post-allocation	Close-out
Timepoint	Visit 1 (day −60–0)	Visit 2 (day 0)	Visit 2 (3 months)	Visit 3 (6 months)
Enrolment				
Eligibility screen	X			
Informed consent	X			
Allocation		X		
Interventions				
Intervention				
Control				
Assessments				
Baseline characteristics	X			
NT-proBNP	X	X		X
Echocardiography	X			X
12 lead electrocardiogram	X			
Vital signs	X	X	X	X
Secondary endpoints		X	X	X

NT-proBNP, N-terminal pro B-type natriuretic peptide.

### Intervention and follow-up

After randomization, patients in the carvedilol-SR group will receive carvedilol-SR 8, 16, 32, or 64 mg once daily for 6 months. Carvedilol-SR (trade name: Dilatrend SR) was manufactured and distributed by Chong Kun Dang Pharmaceutical Corporation in South Korea. The carvedilol dose will be up-titrated at the discretion of the treating physician. The use of beta-blockers other than carvedilol will not be allowed during the study. To avoid drug-drug interactions that may cause confounding effects, drugs with potential pharmacodynamic and pharmacokinetic interference will be prohibited during clinical trials (Table 3).

**Table 3 T3:** Drugs contraindicated during this clinical trial.

Contraindication details
1. Other beta-blockers except the study medication 2. Steroid medication. Locally applied drugs are allowed. 3. Estrogen medications. If necessary, low-dose hormonal therapy can be continued for therapeutic purpose at the same dose during the study period 4. Sympathomimetic drugs such as catecholamines 5. Anti-psychotics, monoamine oxidase inhibitors, lithium, anti-depressants Sedatives and anti-anxiolytics (benzodiazepines and their antagonists, barbiturates, hypnotics such as zolpidem) can be intermittently used according to the physician's decision, while their usage is absolutely prohibited 7 days before the scheduled visits 6. Immunosuppressants 7. Thyroid hormones. If necessary, thyroid hormonal therapy can be prescribed for therapeutic purpose at the same dose during the study period

Non-dihydropyridine calcium channel blockers and antiarrhythmics should be used with caution.

Follow-up visits will be scheduled at 3 (visit 3) and 6 (visit 4) months after randomization (Figure 2 and Table 2). Each clinic visit comprises history-taking, physical examination, laboratory tests, and echocardiography. Drug compliance, adverse effects, and the use of additional concomitant drugs will also be checked. Unscheduled visits will be recorded.

### Study outcomes and variables

The outcomes of this study are presented in Table 4. The primary efficacy outcome will be the time-averaged proportional change in NT-proBNP concentration from baseline through months 3 and 6. The secondary endpoints included the proportion of patients with an NT-proBNP decrease >20% from baseline through months 3 and 6, composite of all-cause mortality and all-cause hospitalization at 6 months. We will also assess changes in BP, HR, New York Heart Association (NYHA) classification, and quality of life at 6 months. Rate of BP control were under controlled will be compared between the two groups, which is defined as SBP <140 mmHg and diastolic BP <90 mmHg at 6 months. In addition, drug adherence and changes in echocardiographic parameters, including left atrial volume index, left ventricular mass index, E/e', e', pulmonary artery systolic pressure, and GLS will be assessed between the two groups. All adverse reactions and the incidence of the following adverse events of special interest during treatment will be assessed: symptomatic hypotension and bradycardia (investigator-reported).

**Table 4 T4:** Primary and secondary endpoints.

	Endpoints detail
Primary endpoint	Time-averaged proportional change in NT-proBNP concentration from baseline through months 3 and 6
Secondary endpoints	Proportion of patients with NT-proBNP decrease >20% from baseline through months 3 and 6
	Composite of all-cause mortality and all-cause hospitalization at 6 months
	Change in blood pressure and heart rate at 6 months
	Rate of blood pressure control at 6 months
	Change in NYHA classification at 6 months
	Change in quality of life assessed by visual analog scale (0–10)
	Drug adherence at 6 months
	Changes in echocardiographic parameter including LAVI, LVMI, E/e’, e’, pulmonary artery systolic pressure and GLS at 6 months

GLS, global longitudinal strain; LAVI, left atrial volume index; LVMI, left ventricular mass index; NT-proBNP, N-terminal pro B-type natriuretic peptide; NYHA, New York Heart Association.

Blood sampling tests at the screening visit will be conducted by the laboratories at each participating institute, which are certified by the Korean Association of Quality Assurance for Clinical Laboratory. Measurement of NT-proBNP by an electro-chemiluminescence immunoassay method using cobas® 8,000 (Roche Diagnostics, Mannheim, Germany) will be performed in a central laboratory at randomization and at 6 months (visit 4). Quality of life will be assessed using a visual analog scale ranging from 0 to 10, with 0 being the worst and 10 being best. Drug adherence will be assessed by “pill count” measurements. The patients will bring the remaining tables to each scheduled visit, and trained and certified researchers will count the number of returned drugs and calculate drug adherence as follows:$$\text{Drug adherence }=\frac{\text{number of pills dispensed-number of pills returned}}{\text{number of days between dispensing date and follow-up date}}$$Baseline echocardiographic data collected within 2 months before randomization will be used. All images will be obtained using a standard ultrasound system with 2.5 MHz probes manufactured by GE, Phillips, and Siemens. Standard techniques will be used to obtain the M-mode, two-dimensional, and Doppler measurements. The LV dimensions, LVEF, and other echocardiographic parameters will be obtained according to the guidelines of American Society of Echocardiography and the European Association of Cardiovascular Imaging (32). Echocardiographic parameters at each institution will be archived in the Digital Imaging and Communications in Medicine format. GLS will be evaluated by a central echocardiography laboratory at the Samsung Medical Center, Seoul, Korea. GLS will be assessed using two-dimensional speckle-tracking echocardiography (2D-STE) on index echocardiography (33). The 2D-STE data will be analyzed using TomTec software (Image Arena 4.6, Munich, Germany) for deformation analyses (2-dimensional cardiac performance analysis) (27). For deformation analysis, endocardial borders are traced on the end-systolic frame in three apical views (4-, 2-, and 3-chamber), with end-systole defined by the QRS complex or as the smallest LV volume during the cardiac cycle. The software tracks speckles along the endocardial border and myocardium throughout the cardiac cycle. The peak longitudinal strain is computed automatically, generating regional data from six segments (anterior, anteroseptal, anterolateral, inferior, inferoseptal, and inferolateral) and an average value for each view. The GLS is determined as the average peak longitudinal strain of 18 LV segments from standard apical views. For patients with SR, analyses will be performed on a single cardiac cycle; for patients with AF, the strain values will be calculated as the average of three cardiac cycles. All strain measurements will be performed by strain specialists who are blinded to other data of each patient. All strain analyses will be performed by a single investigator. In our previous study, intra-observer variability in GLS was assessed in 30 randomly selected patients (34). The coefficient of variation has been identified as 5.8% for the GLS, and the intraclass correlation coefficient was 0.95 for GLS [95% confidence interval (CI), 0.91–0.98].

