
### Sample size and statistical analysis

To date, no previous study has evaluated the effects of carvedilol-SR on HFpEF. Due to the absence of prior research and the pioneering nature of our intervention, a sample size calculation was not conducted at this preliminary stage. As this was a pilot study to explore the benefit of carvedilol-SR for HFpEF, we decided to enroll a total of 100 participants (50 in the carvedilol-SR group and 50 in the control group) across the three institutes, considering the duration of the study and the number of participating hospitals.

Categorical variables will be reported as frequencies (percentages), and continuous variables will be expressed as means ± standard deviations or medians with interquartile ranges. Categorical variables will be compared using Pearson's chi-square test or Fisher's exact test, and continuous variables will be compared using Student's *t*-test or the Mann–Whitney *U*-test.

Primary analysis of the proportional change in NT-proBNP concentration from baseline on a logarithmic scale will be performed using an analysis of covariance model with an adjustment for the baseline value. This will be calculated as the average of the geometric means of NT-proBNP at months 3 and 6 divided by the geometric mean of NT-proBNP at baseline in a natural logarithmic scale (i.e., ratio of geometric means) and summarized as the difference between the treatment groups in the ratio of the geometric means. Cumulative clinical-event rates will be calculated according to the Kaplan–Meier method, and the differences in clinical outcomes between the two treatment groups will be assessed using the log-rank test. Hazard ratios and associated 95% CIs will be calculated using a Cox proportional-hazards model. The incidence of adverse events will be calculated as relative risks with associated 95% CIs.

Missing values due to unevaluable samples or early study discontinuation will not be imputed. Patients with missing baseline NT-proBNP and/or missing 3 and 6 months will not be included in the primary analysis. The data will be primarily analyzed using intention-to-treat analysis, including all randomized patients. We will also perform a per-protocol analysis, which include all randomized patients who receive at least one dose of the study drug during the double-blind period and have no major protocol deviations. Safety outcomes will be analyzed in the safety set of patients who received the trial drug at least once.

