Primarily, we will assess the efficacy of carvedilol-SR on the reduction of NT-proBNP in HFpEF compared with a placebo. In addition, we will evaluate the differential effects of carvedilol-SR on primary outcomes according to prespecified variables, including baseline GLS, and NT-proBNP, LVEF. We planned to use the cutoff value of 14% GLS, taking into account a previous study (28), and also planned to use the median cutoff value of the GLS.

All tests will be two-tailed, and a *P*-value <0.05 will be considered statistically significant. Statistical analyses will be performed using R version 4.2.3 (The R Foundation for Statistical Computing, Vienna, Austria).

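### Month-3 blood pressure and heart rate are scheduled but unused; the month-6 tests leave out patients seen only at month 3, whom a repeated-measures model would keep

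*Protocol article*

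**What the plan says.** All references are to the protocol article.

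- **Endpoint time.** Study outcomes and variables: "We will also assess changes in BP, HR, New York Heart Association (NYHA) classification, and quality of life at 6 months". Table 4 has "Change in blood pressure and heart rate at 6 months" and also gives month 6 for the BP-control rate and NYHA class. Its quality-of-life row gives no time; the text does.
- **Collection.** Table 2 marks vital signs at screening, allocation, month 3 and month 6. A generic row, "Secondary endpoints", is marked at allocation, month 3 and month 6. NYHA class and quality of life have no row of their own.
- **Analysis.** Sample size and statistical analysis compares continuous variables by Student's t-test or the Mann-Whitney U-test. It also says: "Missing values due to unevaluable samples or early study discontinuation will not be imputed". The same section describes the main analysis as intention-to-treat in everyone randomised. It describes no repeated-measures analysis of these endpoints.
- **Size.** "we decided to enroll a total of 100 participants (50 in the carvedilol-SR group and 50 in the control group", and "a sample size calculation was not conducted at this preliminary stage".

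**The concern.** Three stated choices act together: a month-6 endpoint, a test that needs a month-6 value, and no imputation. A patient measured at month 3 who is not seen at month 6 then contributes nothing to the BP and HR comparisons, although a post-randomisation value is on file.

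That has two consequences. First, the set analysed is month-6 completers, not all randomised patients. A completers-only comparison of change scores is safe when loss is unrelated to the patient's own readings. If loss is related to readings already seen at month 3, it can be biased. With a beta-blocker, HR and BP are plausible correlates of leaving. Second, the month-3 readings could support a second, more precise summary of the effect on BP and HR, and nothing in the stated analysis uses them. In a trial of 100 patients sized without a calculation, that is worth having.

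**Working it through.** The plan gives no power, effect size, SD, correlation or dropout figure, so there is nothing of its own to reproduce. From the plan: n = 50 per arm, and "All tests will be two-tailed, and a *P*-value <0.05 will be considered statistically significant". Assumed: equal variances (SD = 1), one common correlation rho among baseline, month 3 and month 6, and a fraction d lost after month 3.

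**1. Cost of losing patients.** The difference detectable with 80% power is (1.960 + 0.842) × sqrt(2/n) = 2.802 × sqrt(2/50) = 0.56 SD of the change score.

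| Lost after month 3 (assumed) | Completers per arm | Detectable difference (SD) | Power at 0.56 SD |
|---|---|---|---|
| 0% | 50 | 0.560 | 80% |
| 5% | 47.5 | 0.575 | 78.0% |
| 10% | 45 | 0.591 | 75.7% |
| 15% | 42.5 | 0.608 | 73.3% |
| 20% | 40 | 0.626 | 70.7% |

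**2. What month 3 recovers for the month-6 contrast.** The partial correlation of months 3 and 6 given baseline is p = rho/(1 + rho). The variance of the repeated-measures estimate relative to completers-only ANCOVA is 1 − d × p².

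- d = 0: ratio 1, no gain.
- d = 0.05, rho = 0.5: p = 0.333; 1 − 0.05 × 0.111 = 0.9944; SE down 0.3%.
- d = 0.20, rho = 0.5: 0.9778; SE down 1.1%.
- d = 0.20, rho = 0.8: p = 0.444; 1 − 0.20 × 0.1975 = 0.9605; SE down 2.0%, an effective 41.7 per arm against 40.

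So month 3 restores little of the power lost in step 1. Moving from a change score to baseline adjustment gives a separate gain, which is not credited here.

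**3. The average of months 3 and 6, a different quantity.**

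- Change scores: 1.5(1 − rho) against 2(1 − rho), a ratio of 0.75 at any rho. The SE is 13.4% lower, equivalent to about 133 patients instead of 100.
- Both baseline-adjusted: (1 + rho)/2 − rho² against 1 − rho².

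| rho | Average | Month 6 | Ratio |
|---|---|---|---|
| 0.4 | 0.54 | 0.84 | 0.64 |
| 0.5 | 0.50 | 0.75 | 0.67 |
| 0.6 | 0.44 | 0.64 | 0.69 |
| 0.7 | 0.36 | 0.51 | 0.71 |

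If months 3 and 6 correlate 0.7 with each other but each only 0.5 with baseline, the adjusted ratio is (0.85 − 0.25)/0.75 = 0.80, so the gain shrinks to 20%.

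For a 0.4 SD effect at both visits with rho = 0.5, baseline-adjusted, the SEs are sqrt(2 × 0.75/50) = 0.173 and sqrt(2 × 0.50/50) = 0.141. Power is 63% for month 6 and 80% for the average. If the month-3 effect is 70% of the month-6 effect, the average has 66%.

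**4. Illustration of bias (simulated, all inputs assumed).** Take a true HR effect of −8 bpm, SD 11, and loss of anyone with month-3 HR below 55 (about 9-12% on carvedilol-SR, 2-3% on placebo). Completers-only ANCOVA gives about −7.5 to −7.6, and a plain change-score comparison about −7.7 to −7.9. A model using month 3 returns −8.0. The SE at 50 per arm with rho = 0.5 is 11 × 0.173 = 1.9 bpm, so the ANCOVA bias of 0.4-0.5 bpm is about a quarter of an SE.

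**The case against.** The best case for the plan is that end-of-treatment change is a proper endpoint. Dose is up-titrated at the physician's discretion, so month 3 may reflect a different treatment state. That stands, and month 6 should remain the endpoint.

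A reader might infer that about a third of the precision of the planned endpoint is thrown away. The documents do not support this. The 29-36% belongs to the two-visit average; for the month-6 contrast the SE gain is 0-2% (step 2).

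A reader might also infer that the BP and HR results cover a different period from the primary endpoint. That cannot be maintained. The primary is defined over months 3 and 6, but the NT-proBNP row of Table 2 is blank at month 3, and Study outcomes and variables places central measurement at randomisation and at 6 months. Whether a month-3 NT-proBNP value will exist is unsettled.

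Other limits also stand:

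- Month-3 collection is explicit for BP and HR only. For NYHA class and quality of life it rests on the generic row, which cannot mean every secondary endpoint at every marked visit: at allocation, adherence and death or hospitalisation cannot yet be assessed.
- The variance figures do not carry over to NYHA class or BP control, which are categorical.
- The dropout example is invented. The article has no withdrawal rule of that kind, and stopping the drug is not leaving follow-up. The model recovers −8.0 because loss was simulated to depend only on observed values.

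Finally, an analysis plan not shown might specify a longitudinal model. But the article itself states the time point, the tests and the missing-data rule, so the point concerns what is written rather than a gap.

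**Conclusion.** The point holds as a modest weakness in secondary endpoints. It is not an error in the primary analysis. As written, BP and HR are compared in month-6 completers only, although month-3 values are scheduled and the analysis is called intention-to-treat in all randomised patients.

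For the month-6 contrast, the main benefit of a repeated-measures model is validity under missing-at-random rather than missing-completely-at-random loss; the SE gain is 0-2% at an assumed 0-20% loss. Loss that depends on unobserved values after month 3 would not be corrected. The sizeable gain, about 25% less variance on change scores or 29-36% baseline-adjusted, applies only to the supportive average and rests on equal correlations (0.4-0.7 for the adjusted figures). It is smaller if the two follow-up visits correlate more strongly with each other than with baseline.

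**What to change.** Analyse BP and HR each with a repeated-measures model of the month-3 and month-6 values containing baseline, visit, treatment and treatment-by-visit.

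- Keep the month-6 contrast as the endpoint.
- Include patients who have only a month-3 value.
- Report the average over months 3 and 6 as a supportive estimate.
- Confirm whether NYHA class and quality of life are recorded at month 3. If so, treat them the same way, with an ordinal model for NYHA class.

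The cost is analysis wording only; the BP and HR measurements are already scheduled. With complete data the month-6 contrast is essentially the baseline-adjusted month-6 comparison. One small downside is that the average includes month 3, when up-titration may be incomplete, so it may be somewhat smaller than the month-6 effect. Reporting both makes that visible.

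A separate point needs reconciling. Intervention and follow-up says "Each clinic visit comprises history-taking, physical examination, laboratory tests, and echocardiography", whereas Table 2 marks echocardiography only at screening and month 6.
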